### Power analyses and analytic plan

To evaluate power for electronic medical record outcomes, we anticipate extracting approximately 1,125 patient charts throughout the study. For purposes of powering provider-level outcomes, we anticipate extracting data allowing within-subjects comparisons among 6 providers per agency, for 54 providers. Provider turnover is estimated to be approximately 30% among CMHA providers and administrators over the trial. Because chart reviews will be pulled via electronic or paper medical records, it is anticipated that provider turnover will not affect the number of charts reviewed. Monte Carlo power analyses were conducted in Mplus using a two- or three-level mixed-effects latent variable design in a multilevel structural equation modeling (MSEM) design [30] to ensure that the anticipated rate of provider and medical record responses were adequate for robust inferences on outcomes, using 1000 replications.

#### *Power for Hypothesis 1*

For *use of CBT strategies*, we examined a three-level mixed effects model assuming agency-level residual ICC of 3%, and provider-level residual ICC of 49%. Three-level generalized linear mixed effects power analysis suggested > 80% power to detect a 25% fixed change (corresponding to a Cohen’s D of 0.123, i.e. a very small effect) in odds of use of JJ COPES + strategies from Usual Care through Sustainment, using 900 observations, given a base rate of 38% use during Usual Care.

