### Eligibility criteria

Agencies are eligible to participate if they provide services to JLIY under the age of 19. Agencies must have at least five eligible providers willing to participate. CMHA administrators will inform their staff about the study and explain to providers that they will be contacted by research staff about participation.

Eligible providers must be employed at a participating agency, have active caseloads of JLIY, be willing to be trained in an evidence-based intervention, and participate in implementation efforts. The study aims to enroll a minimum of 45 providers. Participating providers will provide written consent.

Eligible patient charts are those of youth 19 years of age or younger who have a history of justice involvement. For the purpose of this trial, justice involvement is defined as any history of contact with law enforcement or the court system for illegal behavior that resulted in informal (e.g., police diversion) or formal (e.g., court petition) legal involvement. We will extract, on average, five eligible patient medical records from each of the five providers at each of the nine agencies per time point: this corresponds to approximately 225 charts (5 × 5 × 9) per step and 1,125 charts over the course of the study. Of these, 450 charts will be collected during Usual Care, 225 during Implementation, and 450 during Sustainment.

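### Hypothesis 1: the stated power of more than 80% does not follow from the effect, base rate, sample size and ICCs given beside it; the same inputs give roughly 25 to 37% at two-sided 5%

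*Protocol article*

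**What the plan says.** The section Power for Hypothesis 1 describes a three-level generalized linear mixed model with residual ICCs of 49% for providers and 3% for agencies. It reports more than "80% power to detect a 25% fixed change" and specifies the change as one "in odds of use of JJ COPES + strategies from Usual Care through Sustainment". It equates this with a Cohen's "D of 0.123, i.e. a very small effect". The calculation is described as "using 900 observations" and "given a base rate of 38% use during Usual Care". Alpha, sidedness, the coding of phase and the unit of observation are not given.

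Two other places supply inputs. Eligibility criteria plans five charts from each of five providers at nine agencies per step: 1,125 charts in all, of which 450 fall in Usual Care, 225 in Implementation and 450 in Sustainment. It adds: "The study aims to enroll a minimum of 45 providers". The opening of Power analyses and analytic plan instead bases provider-level power on "within-subjects comparisons among 6 providers per agency, for 54 providers". It says the power was obtained by Monte Carlo simulation in Mplus with 1,000 replications.

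**The concern.** An odds ratio of 1.25 on a binary outcome near 40% is a small effect, and 900 binary observations are few for detecting it. The section gives effect, base rate, number of observations, ICCs and power together, so the claim can be tested from the article alone, and it fails by a wide margin.

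At stake is how the Hypothesis 1 result will be read. A non-significant result would be taken to come from a trial able to detect even a very small change in practice. On the published inputs, the smallest effect detectable with 80% power is about twice as large on the standardised scale.

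**Working it through.** **Inputs.** From Power for Hypothesis 1: base rate 0.38, 25% change in odds, D = 0.123, 900 observations, ICCs 0.49 and 0.03. From Eligibility criteria: 450 Usual Care and 450 Sustainment charts. Their sum matches 900, but the article does not say that this is the split. Assumed, because not stated: two-sided alpha 0.05, with one-sided 0.05 as a variant.

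**1. The effect size reproduces.** ln(1.25) × √3/π = 0.2231 × 0.5513 = 0.123. So the effect is an odds ratio of 1.25. Usual Care odds are 0.38/0.62 = 0.613; 0.613 × 1.25 = 0.766; 0.766/1.766 = 0.434.

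**2. The power does not, with independent charts.** SE(log OR) = √[1/(450 × 0.38 × 0.62) + 1/(450 × 0.434 × 0.566)] = 0.136. Then z = 0.2231/0.136 = 1.64.
- Two-sided: Φ(1.64 − 1.96) = 37.5%.
- One-sided: Φ(1.64 − 1.645) = about 50%.
- 80% power needs about 1,310 charts per phase or, with 450 per phase, an odds ratio of exp(2.80 × 0.136) = 1.46.

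The inferred equal split favours the plan. The two binomial variances are nearly equal, so an uneven split of 900 gives less: 300 v 600 has SE √[1/(300 × 0.2356) + 1/(600 × 0.2456)] = 0.145 and power Φ(1.54 − 1.96) = 34%.

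**3. With the stated ICCs and a conditional odds ratio.** On the logistic latent scale the total variance is 3.29/0.48 = 6.85, so the provider variance is 0.49 × 6.85 = 3.36 and the agency variance 0.03 × 6.85 = 0.206. Averaged over these effects, p(1 − p) is about 0.149. A within-provider comparison then has SE = √[2/(450 × 0.149)] = 0.173, z = 1.29 and two-sided power Φ(1.29 − 1.96) = 25%.

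Simulation of a random-intercept logistic model (45 providers × 20 charts or 54 × 16, 400 to 1,000 replications) gave 23 to 29% two-sided and 33 to 39% one-sided. The odds ratio detectable with 80% power is exp(2.80 × 0.173), about 1.6. On the article's own scale this is D = ln(1.6) × 0.5513 = 0.26, against the stated 0.123.

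**4. Other readings.**

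| Reading | Two-sided | One-sided |
|---|---|---|
| OR 1.25 population-averaged (38% to 43.4%), stated ICCs | 54% | 66% |
| All 1,125 charts, 450 v 675, independent | 43% | 56% |
| All 1,125 charts, 450 v 675, stated ICCs | 30% | 40% |
| 900 charts in each phase, independent | 64% | 75% |
| OR 1.25 per phase step (1.25² = 1.56 overall), stated ICCs | 64 to 79% | 75 to 87% |
| OR 1.25 per phase step, 900 charts over three phases, independent | 84% | 90% |
| 25% relative rise in the proportion (38% to 47.5%), independent | 82% | 89% |
| D = 0.123 on a continuous outcome, residual SD √0.48 | 76% | 85% |

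The last three rows reach 80% only by leaving the stated model. The relative-rise reading also contradicts the stated scale: 47.5% against 38% is an odds ratio of 1.48, or D of about 0.21. The per-step range depends on how charts are spread over phases: 64% with 360/180/360, 73% with 450/225/450, and 77 to 79% with 450 v 450 at 1.56.

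**The case against.** The strongest defence is that the article leaves open several choices that bear on power. Alpha and sidedness are not given, and the hypotheses are directional, so a one-sided test is conceivable. The text says observations, not charts; 900 is also 4 × 225, and Hypothesis 1 concerns sessions. Phase coding is not stated: if 1.25 was the coefficient per phase step, the overall odds ratio is about 1.56, and some one-sided runs with the stated ICCs exceed 80%. Whether the ICCs raise or lower power depends on whether the odds ratio is conditional or population-averaged.

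Much of this stands, and it limits the claim. A reader might infer that 37% is a ceiling. It is not: it holds for two-sided 5% and independent charts, and other odds-ratio readings give 50 to 66%. What does not stand is that any of these choices restores the published sentence. A total odds ratio of 1.25 with 900 binary observations stayed below 80% under every alpha and odds-ratio scale tried. The per-step reading departs from the wording "in odds of use of JJ COPES + strategies from Usual Care through Sustainment", which describes the whole contrast, and its two-sided power is still 64 to 79%.

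Three further inferences are tempting and unsupported.
- That the trial would miss its planned effect about three times in four: the article presents 1.25 as a detectable effect and never as the one expected.
- That Hypothesis 1 is the designated primary outcome: it is listed first under the primary aim but is not labelled so.
- That calendar-time adjustment or the 30% provider turnover lowers power by some known amount: the article does not give enough of the model to put a figure on either.

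The mismatch between 45 and 54 providers is real but secondary. The 45 is a minimum and the 54 an anticipated number, although the chart plan does use five per agency. Both give power far below 80%.

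**Conclusion.** Wrong as written. For an odds ratio of 1.25 from 38% with 900 observations, power at two-sided 5% is about 37% without clustering and about 23 to 29% with the stated ICCs and a conditional odds ratio, against the claimed figure of more than 80%. This rests on an inferred 450 v 450 split and an assumed alpha and sidedness. The shortfall does not depend on either: an uneven split lowers power, and one-sided or population-averaged versions of the total odds ratio reach at most 66% in the checks made.

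The conclusion is that the published inputs and the published power cannot all be right. The article does not show which one is in error, for example whether the 25% was applied to the proportion or to each phase step. Nor does the point show that the trial is too small for the effect it will meet, since no expected effect is stated.

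**What to change.** Withdraw or correct the claim of more than 80% power for a 25% change in odds. Re-run the simulation with the stated ICCs, the actual chart counts and one planned number of providers, reconciling the 45 in Eligibility criteria with the 54 in Power analyses and analytic plan. Report two results: the power at an odds ratio of 1.25 (expected to be about 25% two-sided), and the odds ratio detectable with 80% power (expected to be about 1.6 with the stated ICCs; about 1.46 if charts were independent).

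State the alpha, sidedness, phase coding, unit of observation, and whether the odds ratio is conditional or population-averaged. If the simulation used a per-phase coefficient or session-level observations, say so and give the overall odds ratio and the number of observations simulated.

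The cost is one re-run, a corrected paragraph and a less favourable stated figure. Enrolment does not change.

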## Current study/hypotheses

The primary aim of this study is to evaluate a multi-component implementation strategy on the implementation of evidence-based, outpatient treatment strategies to treat SSITB behaviors in JLIY. We will conduct a stepped wedge cluster-randomized trial with nine Rhode Island CMHAs who provide outpatient therapy to JLIY. Consistent with the Exploration, Preparation, Implementation, and Sustainment (EPIS; [23]) phasic approach to implementation, this protocol consists of one comparison phase (Usual Care) and three active phases: Preparation, Implementation, and Sustainment. The evidence-based intervention being implemented is the Juvenile Justice Coping, Problem-solving, Enhancing life, Safety planning, and Parenting (JJ COPES+) [24] treatment protocol, a cognitive-behavioral therapy protocol that has demonstrated effectiveness with JLIY. We hypothesize that: (1) Receipt of the multi-level implementation strategy will increase the number of sessions that use both general cognitive-behavioral therapy strategies and specific JJ COPES + techniques from the Usual Care to the Implementation and Sustainment Phases; (2) Provider fidelity to the JJ COPES + intervention will achieve acceptable ratings on adherence ratings (80% adherent) and competency ratings (> 33 on the JJ COPES Therapy Rating Scale) during the Implementation Phase and scores will remain in this range through the Sustainment Phase; (3) Number of outpatient sessions attended will significantly increase from Usual Care to the Implementation and Sustainment Phases; (4) The prevalence of youth needing emergent psychiatric care due to experiencing SSITB will significantly decrease from the Usual Care to the Implementation and Sustainment Phases.

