#### *Power for Hypothesis 4*

For *Emergency psychiatric care for SSITB*, we assumed minimal agency- (5%) and provider- (5%) level ICC due to the assignment of cases with suicidal ideation to agencies by Rhode Island courts occurring largely at random. Of patients referred by courts, approximately 10% are expected to be at risk for SSITB. Three-level generalized mixed effects power analysis assessing rates of emergency care for SSITB following intervention, assuming a total of 1,125 observations, suggested 85% power to detect a change of 10% before 5% following implementation.

In addition to these analyses, further exploratory analyses will clarify whether provider characteristics, namely demographics (e.g., sex, race, ethnicity), type of professional degree, years of experience, prior training in SSITB interventions, and time in current position, predict the use of CBT/COPES + strategies and treatment outcomes. Exploratory analyses will also examine whether JJ COPES + fidelity ratings in role-plays predict the use of CBT/COPES + strategies and patient level outcomes.

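### The power above 80% stated for Hypothesis 1 does not follow from its own inputs (odds ratio 1.25 from 38%, 900 charts), which give about 38% or less, and the outcome and contrast it refers to are not fixed

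*Protocol article*

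**What the plan says.** Power for Hypothesis 1 reports: "Three-level generalized linear mixed effects power analysis suggested > 80% power to detect a 25% fixed change". The change is one in odds, for JJ COPES+ strategies, and the paragraph describes it as running "from Usual Care through Sustainment, using 900 observations, given a base rate of 38% use during Usual Care". It equates the effect with a Cohen's D of 0.123 and assumes residual ICCs of 3% (agency) and 49% (provider). The paragraph introduces its outcome as general CBT strategies, but the effect it quotes is for JJ COPES+ strategies.

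Under Current study/hypotheses, H1 is that the strategy "will increase the number of sessions that use both general cognitive-behavioral therapy strategies and specific JJ COPES + techniques"; Implementation and Sustainment are both set against Usual Care. H4 names the same phases in the same way. Patient and provider level outcomes lists general CBT techniques and specific JJ COPES+ skills as two separately coded items.

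Eligibility criteria gives the chart split: "450 charts will be collected during Usual Care, 225 during Implementation, and 450 during Sustainment". Power for Hypothesis 4 uses all of them, "assuming a total of 1,125 observations, suggested 85% power to detect a change of 10% before 5% following implementation", with ICCs of 5% and 5%. The general method is described as follows: "Monte Carlo power analyses were conducted in Mplus using a two- or three-level mixed-effects latent variable design". No alpha or sidedness is given.

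**The concern.** H1 is the first-listed hypothesis and carries the trial's main implementation claim. Its paragraph gives a base rate, an effect on two scales, a number of observations and two ICCs, so the stated power can be checked. An odds ratio of 1.25 from 38% is a difference of about 5 percentage points, and 900 charts look too few to detect that with 80% power.

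If the figure is wrong, a null H1 result would be read as evidence against the strategy, when the trial had less than an even chance of detecting the effect it names. The unclear outcome adds to this, because a reader cannot tell whether the 38% and the power refer to general CBT use, JJ COPES+ use, or both.

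**Working it through.** **Inputs.** Base rate 38%, 25% change in odds, D = 0.123, 900 observations and ICCs 3% and 49% (Power for Hypothesis 1). Charts 450 / 225 / 450, from 9 agencies × 5 providers × 5 charts × 5 steps (Eligibility criteria). Rates 10% and 5%, 1,125 observations and ICCs 5% and 5% (Power for Hypothesis 4). Assumed: two-sided 5%, ICCs on the latent logit scale, no step effects.

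**1. What the 25% means.** D = ln(1.25) × √3/π = 0.2231 × 0.5513 = 0.123. This matches the stated D, so the effect is an odds ratio of 1.25. The odds are 0.38/0.62 = 0.6129; × 1.25 = 0.7661; and 0.7661/1.7661 = 43.4%.

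**2. H1 power without clustering.** Power = Φ[(|p₂ − p₁| − 1.96·SE₀)/SE₁], where SE₀ uses the pooled proportion and SE₁ the separate proportions.
- 450 v 450: SE₀ = 0.03275, SE₁ = 0.03270; (0.0538 − 0.0642)/0.0327 = −0.318; power 37.5%. A one-sided test gives 50%.
- 450 v 675 (all 1,125): SE₀ = 0.02996, SE₁ = 0.02979; (0.0538 − 0.0587)/0.0298 = −0.165; power 43.4% (43.9% with SE₁ throughout).

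**3. H1 power with the stated ICCs.** The total latent variance is (π²/3)/(1 − 0.52) = 6.85, of which 0.21 is agency and 3.36 provider. A linearised three-level logistic model on the 9 × 5 × 5 layout gives these standard errors for the log odds ratio:
- 450 v 450: SE 0.1482; 0.2231/0.1482 − 1.96 = −0.454; power 32.5%.
- All charts pooled: SE 0.1315; 0.2231/0.1315 − 1.96 = −0.263; power 39.6%.

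A 400-replicate simulation, with 38% as the marginal rate and conditional logistic regression within provider, gives 23% for 450 v 450.

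**4. Readings that might give more than 80%.**

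| Reading of 25% | Power, Usual Care and Sustainment charts (900) | Fit with the text |
|---|---|---|
| Odds ratio 1.25 overall | 37.5% unclustered; 32.5% three-level; 23% simulated | Matches odds and D |
| Relative rise, 38% to 47.5% | 82% unclustered; 75% three-level | Odds ratio 1.48, D 0.215; conflicts with both |
| 25 percentage points, 38% to 63% | Near 100% unclustered | Conflicts with odds and D |
| Odds ratio 1.25 per phase, as a trend | 86% (87% with all charts) | Total odds ratio 1.25² = 1.56 (48.9%); not stated |
| Continuous outcome, D on the total SD, compared within provider | 76% | Not the logistic model described |

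**5. H4 as a comparison.** For 10% v 5%, |ln OR| = 0.747.
- 450 v 675: (0.05 − 1.96 × 0.01553)/0.01644 = 1.19, power 88%; three-level SE 0.2456, power 86%; simulation 84.5%. The stated 85% reproduces.
- 450 v 450: 81%, 76% and 74.5% by the same three methods.
- 450 v 225: (0.05 − 1.96 × 0.02257)/0.02028 = 0.28, power 61%; three-level SE 0.3468, power 58%; simulation 60%.

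The same methods that recover H4's figure therefore miss H1's by more than 40 points.

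**6. Chart count and outcome.** 900 equals 450 + 450 (Usual Care plus Sustainment) and also 4 × 225 (four steps). Either way 225 planned charts are missing from H1's calculation but not from H4's, although both hypotheses name the same phases. H1 counts sessions and names two kinds of technique; its power is for the odds of a binary outcome with one base rate.

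**The case against.** **The simulation may have been sound and only its description loose.** This is possible. The relative-rise and per-phase readings come close to or exceed 80%, so a valid Mplus run may lie behind the figure. But the paragraph gives the effect as odds and adds a D that fits only an odds ratio of 1.25. As published, the four figures cannot all be true.

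**A provider ICC of 49% helps a within-provider comparison.** It does for a continuous outcome with D on the total SD, yet that gives only 76% with 900 charts. The stated D is the log odds ratio divided by the residual logistic SD, so this gain does not apply to it.

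**A reader might infer that H4 is also overstated, or that Usual Care v Implementation has far less power than claimed.** The documents do not support this. The hypotheses' wording allows one pooled later-phase comparison, H4's text fits it, and its 85% reproduces. No power is stated anywhere for Implementation alone, so no stated figure is contradicted.

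**A reader might infer that the Implementation charts were dropped from H1.** 450 + 450 fits, but so do four steps of 225, and the text describes a change through Sustainment. This remains an inference.

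**A reader might infer that 38% cannot apply to JJ COPES+ skills before training.** This is not established. The intervention derives from a CBT manual, includes safety planning and problem solving, and usual care may already contain such elements. The defect is that the text does not say which outcome the 38% describes.

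**Conclusion.** H1's power is wrong as written. An odds ratio of 1.25 from 38% with 900 charts gives about 38% power unclustered and about 23–33% with the stated ICCs. All 1,125 charts do not rescue it (43–44% unclustered, 40% three-level). The outcome label and the use of 900 charts also need resolving.

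This rests on a two-sided 5% test (one-sided reaches 50%), on 45 providers as in Eligibility criteria (the power section also mentions 54), and on no step effects. Whether the protocol's power model included step effects is not stated; adding them lowers the pooled three-level power to about 15% for H1 and 39% for H4, so H4's 85% also presumes a model without them.

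The finding does not show that H1 will fail. With the three-level SE of 0.148, 80% power needs a log odds ratio of (1.960 + 0.842) × 0.148 = 0.415, an odds ratio of about 1.5, and training could plausibly produce a change of that size. What is unsupported is the claim to detect 1.25.

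**What to change.** - Reconcile the 25%, the odds scale, D = 0.123 and the power above 80%. Say whether the effect is an overall odds ratio, a per-phase odds ratio or a relative rise, and give the alpha.
- State whether Implementation and Sustainment are pooled or tested separately. Restate H1's power, or its detectable effect, for that contrast with 450 / 225 / 450 charts and the stated ICCs, and explain 900 if it is kept.
- Report this separately for general CBT techniques and JJ COPES+ skills, each with its own Usual Care base rate and on the scale to be analysed.
- Label H4's 85% as Usual Care v Implementation and Sustainment pooled. If Implementation will be tested alone, add that its power is about 58–61%.

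The cost is re-running the simulation and rewording two paragraphs. No extra data are needed, but the stated H1 power becomes less favourable or its target effect becomes larger.

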#### *Power for Hypothesis 2*

Hypothesis 2 refers to the implementation goal of achieving 80% adherence and > 33 scoring on the JJ COPES + Competency Rating Scale via administering the intervention. This implementation check confirms that the intervention is sufficiently effective, and as such, is not subject to frequentist testing. Therefore, there are no power analyses appropriate for this Hypothesis.

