#### **Usual care phase**

During this Phase, agencies will follow usual care practices to serve as the control. Usual care typically includes eclectic therapeutic techniques ranging from supportive therapy to elements of various empirically supported treatments (e.g., cognitive-behavioral therapy). Intake sessions are typically conducted with youth and their caregivers. Follow-up sessions are typically conducted directly with youth and caregivers join sessions at the therapist’s discretion. Depending on which wedge the agency is randomly assigned to, the Usual Care Phase will last between 12 and 33 months.

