#### **Preparation phase**

Community mental health agency providers will be trained in the JJ COPES + intervention during months two and three of the Preparation Phase. Training consists of a combination of didactics (provided in-person or via video), demonstrations, and role plays, consistent with best practices for training [27] and takes approximately five hours to complete.

Following the training, staff will be asked to complete a behavioral rehearsal of JJ COPES + skills as such rehearsals have been demonstrated to be consistent with direct observations [28]. The behavioral rehearsals will be randomly selected from the five possible modules. During the rehearsal, a research assistant will play the role of a client and will enact one of a series of prepared clinical vignettes. Multiple vignettes are available to reduce practice effects. The research assistant will be trained in these vignettes to provide consistency across sites. These will be selected from a battery of standardized vignettes that were developed to be representative of common presenting problems and difficulties faced in facilitating the intervention (e.g., patient has difficulty identifying warning signs, there is a gun in the home). Behavioral rehearsal sessions will be audio recorded for coding by research staff.

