### Patient and provider level outcomes

*Electronic medical record data*. Therapy notes will be coded for evidence of provider-level outcomes, including: (1) use of general techniques consistent with cognitive-behavioral therapy (H1) and (2) use of specific JJ COPES + skills (e.g., safety plan), as well as patient-level outcomes, including: (3) treatment attendance (H3); (4) emergency/crisis service use for STB/NSSI (H4); (5) instances of self-injury (H4); and (6) evidence of suicidal thoughts or attempts (H4).

*Therapist Fidelity and Competency*. To evaluate providers’ fidelity and competence in administering the intervention (H2), we will audio record providers’ completion of behavioral rehearsals of COPES + skills with study staff at 3 time points – one each during the Preparation and Implementation Phases, as well as 9 months into Sustainment. Recordings will be rated by research staff for adherence (using a checklist developed for this trial) and competency; 20% will be rated for inter-rater reliability. Competence will be rated with 8 items created specifically for the JJ COPES + intervention and three items from the Cognitive Behavior Therapy Skillfulness Items [29]. A score > 33 will be used as the criterion to indicate competency on the revised JJ COPES + Competency Rating Scale 12-item version. Providers will be paid $50 for participating in the behavioral rehearsals.

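### H2 is a post-training role-play benchmark without a comparator, so meeting its marks cannot confirm effectiveness, and that assertion is no ground for exempting it from inference

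*Protocol article*

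**What the plan says.** H2 is one of four hypotheses under Current study/hypotheses: "Provider fidelity to the JJ COPES + intervention will achieve acceptable ratings on adherence ratings (80% adherent) and competency ratings" above 33 in the Implementation Phase, after which "scores will remain in this range through the Sustainment Phase". The other three are worded as change from Usual Care; H2 is not.

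Power for Hypothesis 2 restates it as a target: "Hypothesis 2 refers to the implementation goal of achieving 80% adherence and > 33 scoring on the JJ COPES + Competency Rating Scale". It then says "This implementation check confirms that the intervention is sufficiently effective, and as such, is not subject to frequentist testing", and concludes: "Therefore, there are no power analyses appropriate for this Hypothesis".

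On measurement, the Preparation phase section says "Following the training, staff will be asked to complete a behavioral rehearsal", with a research assistant acting the client from a prepared vignette. The Implementation phase section asks providers who received the training for a further rehearsal. Patient and provider level outcomes lists three rehearsals in all, one each in Preparation, Implementation and Sustainment, and says "A score > 33 will be used as the criterion to indicate competency".

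The Discussion presents the trial as a test of whether the strategy can raise fidelity and keep it up.

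**The concern.** The sentence in the power section makes two moves. It treats reaching a pass mark in role-play as confirmation that the intervention works well enough, and it then uses that confirmation as the reason why no test is needed. The first does not follow from a single group measured only after training. The second is circular, because the conclusion is offered as the ground for not examining it.

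Usual care already ranges from "supportive therapy to elements of various empirically supported treatments (e.g., cognitive-behavioral therapy"), and three of the listed competency items come from a general CBT skillfulness measure. Part of a provider's competency score may therefore predate training, and without a Usual Care rehearsal the size of that part is unknown.

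At stake is what may be concluded for a listed hypothesis. Followed as written, the plan would let a result above the marks stand as confirmed effectiveness, when it shows only a level of performance in role-play.

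**Working it through.** The plan gives no sample size, power or precision for H2, so there is no figure to reproduce. The main check sets the passages side by side; the arithmetic only gives scale.

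**1. What the design can identify**

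- *Who is measured:* providers in rehearsals with study staff (Preparation phase; Patient and provider level outcomes).
- *When:* after training in Preparation; in Implementation, among those trained; and in Sustainment. The Sustainment phase section puts the last rehearsal right after consultation ends, whereas Patient and provider level outcomes puts it 9 months into Sustainment. On either reading it follows training.
- *Compared with what:* no Usual Care rehearsal and no untrained group is described.

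The rehearsals can therefore estimate the level of adherence and competency after training, and whether that level holds. They cannot estimate a change from before training, which a claim of improved fidelity needs. They also contain no patient outcome, which a claim of effectiveness needs. The plan itself treats the link from role-play fidelity to strategy use and patient outcomes as exploratory (end of Power for Hypothesis 4), so H2 cannot already have settled it.

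**2. How precise a pass rate would be**

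Inputs from the article:

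- minimum of 45 providers (Eligibility criteria)
- 54 providers and about 30% turnover (Power analyses and analytic plan)
- 9 agencies

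Assumed: an observed pass rate near 80% of providers. This is an illustration. It is not the 80% adherence mark, which the article does not define as a share of providers.

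Wilson 95% interval, with p = x/n and z = 1.96:

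(p + z²/2n ± z√[p(1−p)/n + z²/4n²]) / (1 + z²/n)

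For 36 of 45: centre (0.8 + 0.0427)/1.0854 = 0.776; half-width 1.96 × √(0.003556 + 0.000474)/1.0854 = 0.115; interval 0.66 to 0.89.

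| Providers | Source of n | Passing | Wilson 95% CI |
|---|---|---|---|
| 54 | power section | 43 | 67% to 88% |
| 45 | minimum enrolment | 36 | 66% to 89% |
| 38 | 54 × 0.7 = 37.8 | 30 | 64% to 89% |
| 31 | 45 × 0.7 = 31.5, rounded down | 25 | 64% to 91% |

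The last two rows assume that replacement providers are not rehearsed, which the article does not settle.

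**3. Clustering by agency**

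The article gives no ICC for rehearsal scores. I assume 0 to 0.10, which covers the agency-level values it uses for its other hypotheses (3%, 5%, 10%). With m = 45/9 = 5 providers per agency, the design effect at ICC 0.10 is 1 + (5 − 1) × 0.10 = 1.4. The simple half-width at 80% grows from 1.96√(0.16/45) = 0.117 to 1.96√(0.16 × 1.4/45) = 0.138, or from 11.7 to 13.8 percentage points.

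**The case against.** The strongest reply is that H2 claims less than this point supposes. H1, H3 and H4 are comparisons with Usual Care; H2 is called an implementation goal and an implementation check. A fidelity benchmark needs no untrained arm, and asking untrained staff to show fidelity to a manual they have not been taught has limited meaning, since adherence and 8 of the 11 listed competency items are specific to JJ COPES+. Use of general CBT techniques is compared with Usual Care through chart coding under H1. In a sentence about an implementation check, the word effective may mean only adequately delivered. The article also says that such rehearsals agree with direct observation, and it plans double rating of 20% of recordings.

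Much of this stands. A single-group benchmark without a test is acceptable, and H2 does not touch the sample size or the other three comparisons. But agreement with direct observation supplies no comparator. If adequate delivery was meant, the sentence says something else, and the Discussion's aim of improving fidelity does need a comparison that the rehearsals do not provide.

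Two stronger readings should be resisted. A reader might infer that the plan bars any estimate of uncertainty for H2. It exempts H2 from frequentist testing and power analysis, and is silent on intervals, which an article may leave to the analysis plan. A reader might also infer that H2 will be judged on a group mean, so that it could be declared met while many providers fall short. The article states no such rule, and its above-33 criterion reads naturally as applying to each rated provider.

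**Conclusion.** The point holds as a fault in what the article states, not as a gap in detail. Post-training role-play scores without a comparator can describe whether trained providers reach and hold the marks. They cannot confirm that the intervention is effective or that the strategy improved fidelity, and asserting the former does not justify exempting a listed hypothesis from inference. This rests on the described design alone and needs no numerical assumption.

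The figures show only that sampling error is not negligible. Around an observed pass rate of 80%, the interval runs from roughly 66% to 89% with 45 providers, before any widening for agency clustering. They rest on the assumed pass rate and on the provider counts used. The comparisons under H1, H3 and H4 are unaffected.

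**What to change.** In Power for Hypothesis 2, replace the sentence that claims confirmation with wording such as: *H2 describes whether trained providers reach and hold the pass marks in role-play; it does not test the effect of training or the effectiveness of JJ COPES+.* Bring the Discussion's statement about improving fidelity into line with it.

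State that the above-33 criterion applies to each provider. At each rehearsal time point, report the proportion of providers meeting both marks, with a 95% confidence interval allowing for agency, alongside the mean adherence and competency scores.

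The cost is wording and one descriptive table from recordings already planned; no new data are needed. The downside is a less favourable-sounding claim for H2.
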